### Power calculation

Calculation of the target sample size was based on the patient reported outcomes collected by questionnaire. In order to achieve a power of at least 95% at a type I error rate of  $\alpha = 5\%$  in a two-sided test accounting for the unbalanced group allocation, a minimum of 1,670 patients are needed to be able to detect a small standardized mean difference in group comparisons (Cohen's  $d$  of 0.2) [28] at  $T_2$  following the intention-to-treat principle. Assuming a response rate between 18% and 40% and drop-out rates between 10% and 82% depending on group and phase, a target sample size of approximately 9,000 patients was identified who should be invited to the questionnaire survey. Assuming that around 65% of the invited patients will decline participation and half of them will be followed up, a total of 12,000 patients were targeted (see Figure 1). Because the primary outcome 'time until hospital readmission' is collected from routine data available for the total sample of 12,000 patients from the KKH statutory health insurance, the primary analysis is sufficiently powered to detect even very small effects with a high probability (low type II error).

[figure not shown]

**Figure 1** Expected participant flow for patient-reported outcomes.

## Description of the intervention and control condition

### Intervention condition

The TBHC will follow the concepts of motivational interviewing techniques, individual, collaborative goal setting and shared decision-making. The coach will lead the conversation, but will try to follow a non-directive approach. There will be a minimum frequency defined as one telephone contact every six weeks. The TBHC will have a maximum duration of two years. The intervention will be tailored to chronic diseases that are in need of similar self-management strategies: 1) asthma and COPD, 2) type 2 diabetes, hypertension and coronary artery disease, 3) heart failure and 4) depression and schizophrenia. Each of these disease-specific implementations of the TBHC intervention will have its own treatment manual. These manuals will include information about the inclusion criteria, the scientific background of the campaign and its key contents. All components of the campaign such as the coaching process will be described as well. For example, there will be instructions for specific coaching situations and main topics (for example, diet, immunization and foot control in diabetes and complementary medicine). Even though these instructions exist, the coaching will be tailored to the patients' needs and his individual medical condition. Additionally, the coaches will be supported by a web library and a software program. The web library will provide health information to the coaches to ensure that the information given is evidence-based and up-to-date (for example, by referring to actual

clinical practice guidelines). The software contains available printed information material such as education leaflets for specific conditions, medication plans and weight-control tables that can be sent to the participants by mail. The software also offers a tool to document the process, individual goals, medication, clinical parameters (like HbA1c or blood pressure) and diagnoses.

The coaches will be experienced nurses as well as one nutrition scientist and two coaches who have special expertise with psychiatric patients. They will have been especially trained to carry out the coaching by staff directly qualified by Health Dialog, the company that developed this TBHC in the United States. The coaches will be located in two areas in Germany: one team is operating from Munich and one from Halle/Saale. The coaches will be supervised two to three times a year by two experienced supervisors from the project management group (MH, IB).

### Control condition

The control group will receive no coaching (treatment as usual). It is possible that the control group will receive the same written information material as the intervention group through other employees of the insurance.

### Outcome assessment

#### Primary outcome

The primary outcome is the time from enrollment until hospital readmission within two years. Time until

hospital readmission will be assessed using routine health insurance data of the KKH that records the date of enrollment in the study as well as the dates of hospital stay.

The routine data will be collected and provided by the statutory health insurance. They are generated during the everyday healthcare business and show the actual healthcare situation of the insurant. Every contact within the healthcare system is represented: doctor and hospital visits with ICD code and Operationen- und Prozedurenschlüssel (OPS) code, the German equivalent to the American procedure coding system (PCS), incapacity to work, the medication and much more. The data are not influenced by non-response or recall-bias as they are assessed directly at the healthcare provider. Routine data depicts accountable variables, but not clinical parameters. The validity of routine data in Germany is not proven, yet studies show that the ICD diagnoses are valid in about 97% for heart failure [29,30]. The routine data are read out by the KKH and securely delivered with pseudonymized codes. The outcomes based on routine data include data of the whole randomized sample of approximately 12,000 insurants.

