### Sample procedures

#### Inclusion criteria for patients

Participants should be at least 18 years old and insured of the KKH statutory health insurance. Moreover, included patients will need to have one or more diagnoses of the following: diabetes, coronary artery disease, asthma, hypertension, heart failure, chronic obstructive pulmonary disease (COPD), chronic depression or schizophrenia. Additional inclusion criteria will be used for each target disease. For example, for patients with type 2 diabetes, hypertension or coronary artery diseases, a risk score for hospital readmission will be calculated. Based on various variables from routine data a logistic regression model was designed to predict hospital readmission using SPSS 19. Those variables are, for example, healthcare costs, international classification of diseases (ICD)-diagnoses, age and gender. This model has been validated by analyzing the receiver operating characteristic curve (ROC) [26] and the positive predictive value [27] and showed valid predictions. If the calculated risk for hospital readmission within the next year is higher than 50%, the person will be included in the study. Patients will be excluded from the study if they have insufficient German language skills, are hard of hearing or are not able to read or use a phone.

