### Secondary outcomes

The secondary outcomes include further economic evaluation and the evaluation of patient-reported outcomes.

Secondary outcomes for the health economic evaluation refer to health service use and costs. These include hospital care (hospital admission rates, hospital days and hospital costs) as well as outpatient physician and non-physician services, rehabilitation services and medication. Furthermore, frequency and duration of inability to work as well as mortality will be assessed. Assessment of these outcomes is based on routine data from the KKH.

Moreover, several patient-reported outcomes are used as secondary outcomes, for example, changes in the quality of life (QoL), depression and anxiety, health related behavior and changes in clinical outcomes. The used instruments are mostly validated translations of internationally well-known and standardized instruments with satisfying validity and reliability. The QoL is assessed through the 'Short Form 12 Health Survey' (SF-12) [31] and depression and anxiety are assessed through the 'Hospital Anxiety and Depression Scale' (HADS) [32]. The change of health related behavior is assessed with the 'Alcohol Consumption Questions of the Alcohol Use Disorders Identification Test' (AUDIT-C) [33]. Additionally, a self-developed instrument assesses the amount of smoking, the German version of the 'Medication Adherence Report Scale' (MARS-D) measures medication adherence [34], the amount of exercise is assessed by the 'Freiburg Questionnaire for Physical Activity' (FFKA) [35] and a newly developed instrument assesses the stages of

change. Clinical parameters like glycosylated hemoglobin (HbA1c) and blood pressure are measured with self-developed items.

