### Statistical analysis

Following the intention-to-treat approach we will include all randomized participants in the primary analyses in order to avoid biases such as non-random attrition of participants. As many of the randomized participants decline to take part in the TBHC we run a second intention-to-treat approach, testing the participants versus the control group. Additionally we will perform a sensitivity analysis following the as-treated approach including only participants that have received a minimum of five coaching calls.

Therefore, three different analyses will be performed:

- 1) Intention-to-treat 1: comparing the randomized intervention group (including decliners) versus the control group.
- 2) Intention-to-treat 2: comparing those who took part in the intervention versus the control group (excluding the decliners).
- 3) As-treated: comparing participants who received a minimum of five calls versus the control group.

In order to enhance the comparability of intervention group and control group in the health economic outcomes for analyses 2 and 3, propensity score matching (PSM) will be used to control potential confounding. Routine data from the 12-month period preceding recruitment will be used to match individuals in the intervention group with controls by means of propensity scores. Formally, the propensity score is a person's probability of being assigned to the intervention group given a set of observed covariates. The covariates in the propensity score model will be based on routine data: for example, age, sex, ICD diagnoses, number of days spent in hospital and healthcare costs in the preceding year. The predicted probabilities of unconditional logistic regression models with 'treatment' (intervention versus controls) as dependent variable and the described set of covariates are the basis for the subsequent matching of both groups.

For the primary outcome 'time until hospital readmission' we will use the hazard ratio from a proportional hazard model. Service use and costs will be analyzed by logistic and linear random effects regression models using bootstrapped standard errors.

The secondary outcomes that are patient reported will include different scales, instruments and items with various scale levels. For the analyses of nominal scaled outcomes we will use chi-square tests. Ordinal and interval scaled outcomes will be analyzed using ANOVA

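### Inability to work falls under the whole-sample rule for routine-data outcomes, so insureds who cannot have the outcome dilute its absolute measures and cost power

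*Protocol*

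**What the plan says.** Under Secondary outcomes, the protocol states that "frequency and duration of inability to work as well as mortality will be assessed", and then: "Assessment of these outcomes is based on routine data from the KKH". The Primary outcome section, which describes the routine data, names "incapacity to work, the medication and much more" among their contents and closes with the population statement: "The outcomes based on routine data include data of the whole randomized sample of approximately 12,000 insurants". It makes no exception for any outcome.

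The basic eligibility rule is "Participants should be at least 18 years old and insured of the KKH statutory health insurance", plus at least one listed chronic condition. There is no upper age limit. Further disease-specific criteria are mentioned, but the one described is a readmission risk score, and nothing refers to employment.

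Under Statistical analysis, "we will include all randomized participants in the primary analyses" (intention-to-treat 1, decliners included). The models named for routine-data economic outcomes are these: "Service use and costs will be analyzed by logistic and linear random effects regression models using bootstrapped standard errors". No section defines a population at risk for inability to work.

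**The concern.** A whole-sample population suits hospital stays, costs and mortality, because any insured person can have them. Inability to work is different: by its meaning it needs someone who works, or who holds a status in which the insurer records it. Pensioners and other insureds without a job have no spell and no days whatever their health. Counted with everyone else, they are structural zeros.

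Two things are at stake. First, the reported frequency, mean days and absolute arm difference no longer describe people who could be unable to work. The zeros also add variance without information, so a real effect is harder to detect. Second, someone who leaves work because of illness stops producing inability-to-work days and so looks improved. Unless leaving employment is reported by arm, that cannot be told apart from a true reduction.

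**Working it through.** **The plan's own figure.** The 12,000 can be rebuilt from the Power calculation and Treatment allocation sections: about 9,000 questionnaire invitations, 5:1 allocation, about 65% declining and half of the decliners followed up. The invited fraction is 1/6 + 5/6 × (0.35 + 0.65 × 0.5) = 0.7292, and 9,000 / 0.7292 = 12,343, within 3% of 12,000. At 5:1, 12,000 means about 10,000 versus 2,000.

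**Assumed inputs.** The protocol gives no working share, spell rate, mean, SD or effect for this outcome. I assume:
- working share p = 30%, 50% or 70%, equal in both arms;
- any spell among workers: 50% in controls, 45% under intervention;
- days among workers: mean μ = 20, SD s = 40, difference d = 3;
- insureds not in work enter as zeros;
- two-sided 5% test, normal approximation.

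**Formulas.** Whole-sample mean = p·μ. Whole-sample difference = p·d. Whole-sample variance = p·s² + p(1−p)·μ². The test statistic in the whole sample, divided by that among workers only, is 1/√(1 + (1−p)·μ²/s²). This is below 1 for every p below 1. The direction is therefore certain, and only the size depends on the assumptions.

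**Worked case, p = 50%.**
- Any spell, workers (1,000 vs 5,000): SE = √(0.25/1,000 + 0.2475/5,000) = 0.01731; z = 0.05/0.01731 = 2.89; power 82%.
- Any spell, whole sample (25% vs 22.5%; 2,000 vs 10,000): SE = √(0.1875/2,000 + 0.174375/10,000) = 0.01054; z = 0.025/0.01054 = 2.37; power 66%.
- Days, workers: SE = 40 × √(1/1,000 + 1/5,000) = 1.386; z = 3/1.386 = 2.17; power 58%.
- Days, whole sample: SD = √(0.5 × 1,600 + 0.25 × 400) = 30; SE = 30 × √(1/2,000 + 1/10,000) = 0.735; z = 1.5/0.735 = 2.04; power 53%.

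**All three shares.**

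| Working share | Risk difference, whole sample (workers: 5.0 points) | Odds ratio, whole sample (workers: 0.82) | Power, any spell: workers / whole sample | Days difference, whole sample (workers: 3.0) | Power, days: workers / whole sample |
|---|---|---|---|---|---|
| 30% | 1.5 points | 0.88 | 61% / 41% | 0.9 | 39% / 34% |
| 50% | 2.5 points | 0.87 | 82% / 66% | 1.5 | 58% / 53% |
| 70% | 3.5 points | 0.85 | 93% / 85% | 2.1 | 73% / 70% |

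**Sensitivity.** With 40 versus 36 days and SD 70 among workers, power at working shares of 20%, 40%, 60% and 80% is 18%, 31%, 44% and 55% in workers, against 15%, 27%, 40% and 53% in the whole sample. The loss is again modest for days.

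**What is not diluted.** The risk ratio stays at 0.45/0.50 = 0.90 in both populations, because p cancels. The same holds for a ratio of means when the working share is balanced between arms. Mean length per spell is also unaffected.

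**The case against.** The strongest reply is that the quoted sentence describes data coverage: it closes a paragraph on where routine data come from and why non-response does not affect them. It is not worded as an analysis-set rule. The second intention-to-treat analysis and the as-treated analysis themselves use subsets. On this view the handling of people without a job is simply left open, and a statistical analysis plan could settle it. Part of this stands: the protocol nowhere says that such insureds are coded as zero, so that step is an inference. But the document is not silent on the population. It names one for routine-data outcomes, without exception, and that population includes people who cannot have this outcome.

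A second reply is that a per-insured average is a sensible quantity for an insurer's economic evaluation. That stands, and the fix keeps it. A reader might infer that the whole-sample result is biased by 30% to 70%. The documents do not support that. Randomisation leaves the intention-to-treat 1 contrast unbiased for the average over insured persons. The shrinkage is relative to the effect among workers, and the percentages only restate assumed working shares.

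Third, the any-spell losses rest on a generous effect. If decliners gain nothing, a 5-point effect over the whole intervention arm needs 5/0.35, about 14 points, among the 35% who take part. With a 2-point effect among workers and a 50% share, z is 0.02/0.01732 = 1.15 in workers and 0.01/0.01058 = 0.95 in the whole sample, so power is about 21% versus 16%: low either way. The protocol claims no power for this outcome. This limits the practical gain but does not reverse it.

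Finally, it is true that the protocol does not state who can have an inability-to-work record, nor that an employment field is available. The first follows from the meaning of the outcome, and the second is an assumption.

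**Conclusion.** The point holds as one of dilution, lost power and interpretation for a single secondary outcome. Absolute frequency, mean days per person and the absolute arm difference equal the working share times their values among workers. The odds ratio moves towards 1, and power is lower at every working share below 1. Under the assumed values, with shares of 30% to 70%, the loss is about 8 to 20 percentage points for any spell and 3 to 5 points for days.

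This rests on zero coding of insureds not in work, balanced employment between arms, and rates and effects that the protocol does not give. It does not extend to ratios of means or risks, to length per spell, or to the primary outcome. The change is a worthwhile, cheap improvement and does not correct an invalid comparison.

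**What to change.** Exempt inability to work from the whole-sample statement and define its analysis as follows:

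- **Main analysis:** intention-to-treat 1 by randomised arm, among insureds who at randomisation were in work or otherwise in a status for which the insurer records inability to work. This is a baseline subset, so the randomised comparison is kept.
- **Supplement:** the whole-sample, per-insured result, for the economic evaluation as a cost component.
- **Alongside:** leaving employment during follow-up, by arm, so that ill-health exit from work is not read as fewer sick days.
- **Sensitivity analysis only:** a rate per time in employment. That denominator arises after randomisation and coaching could change it, so it should not carry the main result.

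The cost is a few sentences in the analysis section and one baseline employment or insurance status field from the insurer, whose availability is assumed here and must be confirmed. No extra patients are needed. The downside is a smaller analysis set for this outcome and dependence on the quality of that status field.

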### Secondary outcomes

The secondary outcomes include further economic evaluation and the evaluation of patient-reported outcomes.

Secondary outcomes for the health economic evaluation refer to health service use and costs. These include hospital care (hospital admission rates, hospital days and hospital costs) as well as outpatient physician and non-physician services, rehabilitation services and medication. Furthermore, frequency and duration of inability to work as well as mortality will be assessed. Assessment of these outcomes is based on routine data from the KKH.

Moreover, several patient-reported outcomes are used as secondary outcomes, for example, changes in the quality of life (QoL), depression and anxiety, health related behavior and changes in clinical outcomes. The used instruments are mostly validated translations of internationally well-known and standardized instruments with satisfying validity and reliability. The QoL is assessed through the 'Short Form 12 Health Survey' (SF-12) [31] and depression and anxiety are assessed through the 'Hospital Anxiety and Depression Scale' (HADS) [32]. The change of health related behavior is assessed with the 'Alcohol Consumption Questions of the Alcohol Use Disorders Identification Test' (AUDIT-C) [33]. Additionally, a self-developed instrument assesses the amount of smoking, the German version of the 'Medication Adherence Report Scale' (MARS-D) measures medication adherence [34], the amount of exercise is assessed by the 'Freiburg Questionnaire for Physical Activity' (FFKA) [35] and a newly developed instrument assesses the stages of

change. Clinical parameters like glycosylated hemoglobin (HbA1c) and blood pressure are measured with self-developed items.

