## Abstract

**Background:** The rising prevalence of chronic conditions constitutes a major burden for patients and healthcare systems and is predicted to increase in the upcoming decades. Improving the self-management skills of patients is a strategy to steer against this burden. This could lead to better outcomes and lower healthcare costs. Health coaching is one method for enhancing the self-management of patients and can be delivered by phone. The effects of telephone-based health coaching are promising, but still inconclusive. Economic evaluations and studies examining the transferability of effects to different healthcare systems are still rare. Aim of this study is to evaluate telephone-based health coaching for chronically ill patients in Germany.

**Methods/Design:** The study is a prospective randomized controlled trial comparing the effects of telephone-based health coaching with usual care during a 4-year time period. Data are collected at baseline and after 12, 24 and 36 months. Patients are selected based on one of the following chronic conditions: diabetes, coronary artery disease, asthma, hypertension, heart failure, COPD, chronic depression or schizophrenia. The health coaching intervention is carried out by trained nurses employed by a German statutory health insurance. The frequency and the topics of the health coaching are manual-based but tailored to the patients' needs and medical condition, following the concepts of motivational interviewing, shared decision-making and evidence-based-medicine. Approximately 12,000 insurants will be enrolled and randomized into intervention and control groups. Primary outcome is the time until hospital readmission within two years after enrolling in the health coaching, assessed by routine data. Secondary outcomes are patient-reported outcomes like changes in quality of life, depression and anxiety and clinical values assessed with questionnaires. Additional secondary outcomes are further economic evaluations like health service use as well as costs and hospital readmission rates. The statistical analyses includes intention-to-treat and as-treated principles. The recruitment will be completed in September 2014.

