### Telephone-based health coaching

There are many ways to deliver health coaching; one way is coaching by phone, which allows reaching even rural areas and impaired patients. The increasing number of studies that evaluate telephone-based health coaching (TBHC) for chronically ill patients shows promising but also conflicting results. For example, participants of TBHC

have reduced diabetes symptoms as well as lowering depressive symptoms [13] and gaining a better total cholesterol and LDL-value [14]. It seems that TBHC has the potential to reduce the rate of coronary events, like myocardial infarction, coronary artery bypass graft and cardiovascular death [15]. However, there are also some studies showing that there are no improvements regarding targeted clinical outcomes [16]. Furthermore, TBHC can help participants change health behavior [17], enhance self-rated health [18], social functioning, self-efficacy, patient activation and perceived health [13,17].

Economic evaluations are rare and still contradictory to some extent. Studies show that TBHC can reduce the number of contacts to the general practitioner [19], hospitalization rates and healthcare costs [11]. However, other studies show only modest effects on hospital admissions or emergency room visits. Also, these studies show no reduction of utilization and costs accompanied by high costs for the admission of the coaching [20,21].

In summary, the results of studies evaluating TBHC are ambiguous. The clearest effects can be observed with psychosocial and self-reported outcomes, like self-efficacy and perceived health. Considering economic effects and clinical outcomes, results of empirical studies are still inconsistent.

In Germany, health coaching is an innovative approach, and the number of studies evaluating TBHC in Germany is very limited. Long-term effects and cost-effectiveness have not been analyzed yet. However, the patients' acceptance of the intervention is good [22-24]. The TBHC used in this study is based on a TBHC service developed by Health Dialog [11,25] and was implemented by Kaufmännische Krankenkasse Hannover (KKH), a statutory health insurance, in 2007. The coaching was adapted to the German patients' requirements after assessing the needs in a previous study [22].

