### Objectives

The objective of the trial is to evaluate the effectiveness of TBHC for patients of a health insurance fund against usual care regarding its impact on healthcare costs and patient-reported outcomes. The primary hypothesis is that TBHC will extend the time period until hospital readmission. Secondly, we hypothesize that TBHC will reduce healthcare costs and hospital readmission rates.

Furthermore, the positive impact of TBHC on patient-reported outcomes like quality of life (QoL), depression and anxiety, health behavior, health literacy, patient activation and the evaluation of TBHC by participants will be evaluated. We also expect TBHC to increase quality of life and decrease psychological distress such as depression or anxiety.

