## Discussion

This study is a 4-year RCT that examines the economic and psychosocial evaluation of a telephone-based health coaching. The evaluated intervention is a health coaching delivered by phone by specially trained nurses. It focuses on lifestyle change using motivational interviewing techniques combined with individual goal setting. The coaching is manualized and computer supported.

As there are just few publications about the health economic evaluation of telephone-based health coaching (TBHC) programs, and especially few about TBHC in the German healthcare system, this trial can fill the existing gap. Our findings will be relevant for future health coaching programs as potential cost savings are interesting for statutory health insurances.

Nevertheless, there are some limitations to this study: Randomization took place before informed consent was obtained from participants. As participants and decliners are likely to be different, this may cause bias with respect to the groups compared in the intention-to-treat-2 and the as-treated analysis. Although we apply advanced statistical methods, potential confounding cannot be ruled out completely. Another limitation could be the unsure validity of the routine data, but an extensive literature research revealed that the quality of routine data in Germany is good [29]. The generalizability of the secondary patient reported outcomes may be limited by social desirability, because the statutory health insurance is sending out the questionnaires. To prevent this bias we assured the insurants in the cover letter that non-response will definitely have no negative consequences. Another possible limitation is the quality of the items questioning the clinical parameters like HbA1c. They are patient reported on an ordinal scale, which means they are prone to be inexact. To approach this problem we take advantage of the opportunity to use the software data available for the participant group as well.

Since the amount of studies evaluating psychological and economic outcomes of health coaching interventions are rare, our study will provide evidence, which is needed for different healthcare bodies. The study's outcome will

help determine whether TBHC is a promising tool to enhance the self-management of chronically ill patients and thus reduce costs, increase quality of life and change clinical parameters.

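### As defined, the cost outcome does not count the coaching itself, so it can show an effect on healthcare-service costs but not a net saving to the insurer

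*Protocol*

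**What the plan says.** Under Objectives the Protocol states a directional cost hypothesis: "Secondly, we hypothesize that TBHC will reduce healthcare costs and hospital readmission rates".

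Under Secondary outcomes it names what the health economic evaluation covers: "These include hospital care (hospital admission rates, hospital days and hospital costs) as well as outpatient physician and non-physician services, rehabilitation services and medication". Inability to work and mortality are added, and one data source is given: "Assessment of these outcomes is based on routine data from the KKH". Under Primary outcome those routine data are described: "They are generated during the everyday healthcare business and show the actual healthcare situation of the insurant".

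The Abstract says who delivers the coaching: "The health coaching intervention is carried out by trained nurses employed by a German statutory health insurance". Control condition says that controls are not coached. Statistical analysis gives random effects regression with bootstrapped standard errors for service use and costs, and mentions no programme cost.

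Two sections bear on how the result will be read. The Background, under Telephone-based health coaching, reports that in some earlier studies utilization and costs did not fall, "accompanied by high costs for the admission of the coaching". The Discussion says that "potential cost savings are interesting for statutory health insurances" and that the trial will help decide whether coaching can reduce costs.

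**The concern.** The payer is also the provider of the intervention. Work done by the insurer's own employees is not a hospital, outpatient, rehabilitation or medication item, and nothing in the Protocol suggests that it enters the routine data as one. Acquisition calls, supervision, software, the web library and mailed material are likewise uncosted. The intervention arm would be credited with any fall in claims and not charged for the programme that produced it.

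At stake is the payer-facing conclusion. A fall in claims smaller than the cost of the coaching would appear as lower cost while the insurer's total spending rose. The Protocol's own Background shows awareness that programme cost can decide this question.

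**Working it through.** The Protocol states no coaching cost, cost standard deviation or expected cost effect, so there is no figure of its own to reproduce. The check has four steps.

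**1. Is the coaching inside the cost outcome?** The listed components are hospital, outpatient physician and non-physician services, rehabilitation and medication. The source is routine data arising from ordinary care. The coaching comes from the insurer's employed staff (Abstract) and fits none of these components. No other section costs it, adds it to the outcome, or limits the hypothesis to costs excluding the programme.

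**2. Which arm carries the missing cost?** Inputs: 12,000 randomized and about 65% declining (Power calculation); 5:1 allocation (Treatment allocation).
- Intervention: 12,000 × 5/6 = 10,000. Control: 2,000.
- Coached: 0.35 × 10,000 = 3,500. Decliners: 6,500, of whom half (3,250) are followed up by questionnaire.
- Consistency check: 3,500 + 3,250 + 2,000 = 8,750, in line with the roughly 9,000 to be invited to the survey.

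Calls fall on the intervention arm only. Controls may be sent written material by other insurance employees (Control condition). That is also uncounted, but likely minor.

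**3. How much is missing?** At the minimum of one contact per six weeks over the two-year maximum, the number of calls is 104/6 = 17.3, about 17. This applies only to someone coached for the full two years at that frequency; Study design says the length is tailored and only capped. Let c be the coaching cost per participant:
- Intention-to-treat 1: 0.35 × c per person randomized to intervention, plus the invitation and acquisition cost, which decliners also incur.
- Intention-to-treat 2 and as-treated: c in full.

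For an assumed c of EUR 100 to 1,000 (not from the documents), the missing amount in intention-to-treat 1 is EUR 35 to 350 per person randomized to intervention.

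**4. Could that change a conclusion?** Suppose the true net difference is zero, so that coaching cuts claims by exactly what it costs. With SE = SD × √(1/n₁ + 1/n₂), the chance that the claims-only comparison shows a significant reduction is Φ(missing cost/SE − 1.96). Without the omission it would be 2.5% in that direction.

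With an assumed SD of EUR 10,000:
- Intention-to-treat 1: SE = 10,000 × √(1/10,000 + 1/2,000) = 245. For c = 500: 175/245 = 0.71, and Φ(0.71 − 1.96) = 10.6%.
- Intention-to-treat 2: SE = 10,000 × √(1/3,500 + 1/2,000) = 280. For c = 500: 500/280 = 1.78, and Φ(1.78 − 1.96) = 43.0%.

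| Assumed SD (EUR) | Assumed c (EUR) | Intention-to-treat 1 | Intention-to-treat 2 |
|---|---|---|---|
| 10,000 | 100 | 3.5% | 5.4% |
| 10,000 | 250 | 5.4% | 14.3% |
| 10,000 | 500 | 10.6% | 43.0% |
| 10,000 | 1,000 | 29.8% | 94.6% |
| 5,000 | 500 | 29.8% | 94.6% |
| 15,000 | 500 | 6.9% | 22.0% |

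This is a simple normal approximation. It ignores acquisition cost, the propensity matching, any residual confounding and the Bonferroni correction. In each case the claims reduction is real; the error lies in reading it as a net saving.

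**The case against.** The best defence is that the Protocol never says coaching costs are excluded. The list of components is introduced as an inclusive one, the routine data are described as holding more than the items named, and a health-economic analysis plan not shown here could add programme cost. Perspective and unit costs are often left to such a plan. This stands against any claim of deliberate exclusion. It does not remove the point, because Secondary outcomes fixes both the components and the source, and as written neither captures the intervention.

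The second defence also stands: the effect of coaching on downstream service costs is a legitimate question, and in intention-to-treat 1 randomization supports the answer. A reader might infer that the cost comparison itself is biased. It is not, if it is labelled as service cost. What fails is the step from that comparison to savings for the insurer, and the Discussion invites that step.

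A reader might also infer that every omitted cost sits in the intervention arm, or might put a total in millions of euros on the omission. Control condition allows some uncounted written material for controls. A total would need an assumed price per call and every participant staying the two-year maximum, whereas the as-treated threshold of five calls implies that some receive fewer. The documents support neither inference.

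**Conclusion.** The point holds in this form. The cost outcome measures healthcare-service cost, and the Protocol ties its result to cost savings for insurers without counting what the coaching costs. Read as payer spending, the comparison favours coaching, because the main omitted cost falls on the intervention arm.

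The size cannot be established. About 35% of the per-participant coaching cost, plus acquisition, is missing per person randomized to intervention in intention-to-treat 1, and all of it in the other two analyses. The 35% rests on the Protocol's planned decline rate. Every euro figure above and the cost SD are assumptions, so the probabilities show only that the omission could matter under plausible values. The absence of coaching from the routine data is inferred from the stated components and source, and the employment of the coaches from the Abstract alone. The primary outcome is unaffected.

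**What to change.** In Secondary outcomes, add programme cost as a cost component: coach time from call records at the insurer's staff rate, acquisition calls, supervision, software and mailings, plus any material sent to controls.

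In intention-to-treat 1, charge it across everyone randomized to intervention, including the acquisition cost of decliners. In all three analyses, report costs with and without programme cost, label the claims-only result as healthcare-service cost, and base any cost-saving conclusion on the net figure.

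Much of the information should already exist: the as-treated analysis needs call counts per participant, and the coaching software documents the process. The price is a little more analysis work and a less favourable reported saving. Randomization, follow-up and the primary analysis do not change.
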